#### Guidelines for stopping treatment

A permanent discontinuation of trial medication should be considered only when one of the following conditions exists:
A patient decides that it is in her/his best interest to withdraw her/his consent to continue study treatmentA serious adverse event occurs that is suspected to be related to trial medication and/or prevents patient’s continuation on study medicationAn investigator considers it advisable for sound, explicit, and documented clinical reasons

In all of these cases, the scheduled follow-up visits will be continued as planned by the study protocol. A patient will be considered discontinued from the study only if he or she withdraws their consent to be followed by the participating centre, or he or she is lost to follow-up after exhausting all means of contact. Surgical correction of CCM during follow-up shall require the patient’s discontinuation from the study.

In the case of discontinuation, the status of the patient at the last visit or last available contact will be used for the final analysis. Vital status may be ascertained through public records, in the case of failure of all other methods of contact.

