### Design

The study protocol was designed according to the real-life management of patients with FCCMs (Fig. 1). Treat_CCM is a multicentre, open-label, randomized controlled trial (PROBE design, prospective randomized open trial with blinded evaluation of outcomes) in patients with FCCMs. Patients, fully informed of the trial, after signing the informed consent form are randomly assigned by computer, upon completing the randomization electronic case report form (e-CRF), in a 2:1 ratio to the study groups: one receiving *propranolol* in addition to standard care; the other, *controls*, receiving standard care alone (Fig. 1). The study will be open-label since the implementation of blinding would require placebo and ad hoc procedures with costs non-sustainable in a pilot study fully supported by public funding. In order to reduce possible biases, a PROBE design will be applied so that each MRI examination will be centrally read after de-identification, and all adverse clinical events will be centrally adjudicated. It should be pointed out that by no means will surgery, whenever indicated, be delayed and/or avoided because of study treatment allocation.

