### Outcomes

The primary endpoint will be the new occurrence of clinical symptomatic CCM-related events, which are intracerebral haemorrhage (ICH) and focal neurological deficits (FND), as defined by Al-Shahi Salman et al. [30], excluding seizures.

Secondary endpoints include the following:
Microvascular haemorrhages as assessed by MRI analysis of brain tissue magnetic susceptibility, a biophysical property proportional to the local iron content (susceptibility weighted imaging (SWI) and quantitative susceptibility mapping (QSM)), and dynamic contrast enhanced permeability (DCEP).Clinical outcomes, other than ICH and FND, such as global disability, health-related quality of life, depression severity, and two types of anxiety (state anxiety, or anxiety about an event, and trait anxiety, or anxiety personal level), as assessed by the SF-36, BDI-II and State-Trait Anxiety Inventory (STAI) questionnaires.Seizures.Different MRI CCM characteristics, such as location (cerebellum, brainstem, right/left hemispheric white matter, right/left basal ganglia), diameter, length, and MRI signal appearance. Lesions with previous surgical treatment will be excluded from imaging analysis.Appearance of de novo CCM lesions at MRI.

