#### Statistical analyses

The main analysis will be performed according to an intention-to-treat (ITT) approach. Therefore, all patients randomized in the study will be included in the analysis. As we cannot conduct inferential statistics on the data collected in the pilot study, we will only compare the proportions of adverse events between the groups to assess the safety of propranolol [42]. A per-protocol analysis is foreseen.

Baseline characteristics will be presented by treatment groups, and descriptive statistics will be performed to assess the success of randomization. Kaplan–Meier curves will be constructed to illustrate the occurrence of adverse events in the study over time.

Concerning the analysis of this pilot study, we are only interested in whether the treatment estimate is larger or smaller than zero. Consequently, it is not necessary to formally undertake a hypothesis test of the results. An extension of the trial in the case of encouraging preliminary results is foreseen. Special care will be paid to the biologic consistency of the different endpoints, even if none of them will yield statistically significant differences.

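### The protocol both forbids and requires ending study participation at CCM surgery; if follow-up does end there, the analysis is ITT in membership but not in follow-up

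*Protocol article*

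**What the plan says.** The protocol article, Guidelines for stopping treatment, separates stopping the trial medication from leaving the study. For patients who stop medication: "In all of these cases, the scheduled follow-up visits will be continued as planned by the study protocol". Leaving the study is then defined by a closed list of two grounds. The first reads: "A patient will be considered discontinued from the study only if he or she withdraws their consent to be followed by the participating centre". The second is that the patient can no longer be reached by any route. The sentence that follows adds a third: "Surgical correction of CCM during follow-up shall require the patient’s discontinuation from the study". For discontinued patients, "the status of the patient at the last visit or last available contact will be used for the final analysis".

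Three other sections bear on this:
- Statistical analyses: "The main analysis will be performed according to an intention-to-treat (ITT) approach". It includes every randomized patient, plans Kaplan–Meier curves, and reads the result by whether the treatment estimate lies above or below zero.
- Design: the trial is open-label with blinded endpoint evaluation, and "by no means will surgery, whenever indicated, be delayed and/or avoided because of study treatment allocation".
- Outcomes: the primary endpoint is new ICH or FND, with seizures excluded. For MRI, "Lesions with previous surgical treatment will be excluded from imaging analysis".

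**The concern.** A closed list of two grounds is followed at once by a compulsory third, so sites could follow either rule.

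If surgery ends participation, the exit is tied to the disease. Background and rationale gives the indications as seizures that resist treatment, deficits caused by repeated bleeding, and mass effect. It also says that surgery cannot clear the multiple lesions of the familial form, so an operated patient remains at risk of the primary endpoint. Seizures are not primary events. A patient operated on for seizures or mass effect can therefore leave before any ICH or FND and be carried forward as event-free; in a Kaplan–Meier curve that patient would presumably be censored, plausibly informatively.

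Later MRI, seizure and questionnaire data are lost for the same patients. This matters because step 2 of the design depends on both the clinical comparison and the MRI findings of step 1.

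**Working it through.** **Inputs.** Two-year control risk 10.1% and target reduction 50%, giving 5.05% (Sample size). 40 propranolol and 20 control patients (Design). The documents give no rate of CCM surgery during follow-up; 2% to 10% over two years is assumed below.

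**The plan's own figure.** With 2:1 allocation, one-sided α 0.05, 80% power and unpooled variance:

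n(control) = (1.6449 + 0.8416)² × [0.101 × 0.899 + 0.0505 × 0.9495 / 2] / 0.0505² = 278.2

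Taking 278 per control unit gives 3 × 278 = 834, the stated total. The inputs are therefore read as the plan intends. The figure itself does not decide this point.

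**The sentences side by side.**

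| Situation | Rule in the same section |
|---|---|
| Trial medication stopped | Visits continue |
| Study discontinuation, definition | Only consent withdrawal or loss to follow-up |
| CCM surgery | Study discontinuation required |
| Data used after discontinuation | Last known status |

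Rows two and three conflict. Rows three and four together determine what the ITT analysis contains for an operated patient: the patient, with events up to surgery and none after it.

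**Expected events.** Control: 20 × 0.101 = 2.02. Propranolol: 40 × 0.101 = 4.04 with no effect, or 40 × 0.0505 = 2.02 with the target effect.

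**Weight of one unobserved event.** Control: 1/20 = 5.0 points. Propranolol: 1/40 = 2.5 points. Target difference: 10.1 − 5.05 = 5.05 points.

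| True counts (propranolol v control) | Unobserved event | Observed counts | Risk difference (points) | RR |
|---|---|---|---|---|
| 4/40 v 2/20 | control | 4/40 v 1/20 | 0 to +5.0 | 1.0 to 2.0 |
| 4/40 v 2/20 | propranolol | 3/40 v 2/20 | 0 to −2.5 | 1.0 to 0.75 |
| 2/40 v 2/20 | control | 2/40 v 1/20 | −5.0 to 0 | 0.5 to 1.0 |
| 3/40 v 2/20 | control | 3/40 v 1/20 | −2.5 to +2.5 | 0.75 to 1.5 |

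Only the last row reverses the sign. The first two move the estimate off the null, and the third removes the target effect.

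**How likely is a lost event?** Assumed surgery rates of 2%, 5% and 10% give 60 × 0.02 = 1.2, 60 × 0.05 = 3 and 60 × 0.10 = 6 exits. An exit hides a primary event only if a patient who was event-free at surgery then has one before month 24. Suppose three such patients are operated on at mid-follow-up, each with a residual risk of about 5% (half of 10.1%). The expected number of lost events is 3 × 0.05 = 0.15, and the chance of at least one is 1 − 0.95³ = 14%. At three times that risk it is 1 − 0.85³ = 39%.

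**The case against.** The strongest defence is that little primary-endpoint information is lost. A patient operated on after a new haemorrhage or deficit during follow-up has already had a primary event, and the last-status rule keeps it. Adjudication is blinded, and the Design section guards against allocation delaying or preventing surgery. The trial is a pilot without formal testing, and chance is at least as large a source of error: at 4/40 v 2/20 the 80% one-sided half-width is 0.8416 × √[0.1 × 0.9 × (1/40 + 1/20)] = 6.9 points.

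The first of these stands and limits the size of the problem. The others do not remove it. Adjudicators cannot assess events that nobody collects. The Design sentence addresses surgery being delayed or avoided, not surgery being chosen more readily in one arm, and it recovers no later outcome. Chance error does not excuse an avoidable gap.

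The surgery sentence might also be meant to cover stopping the drug only. Its wording says otherwise, the section treats the two separately, and controls have no trial medication to stop. If that was the intent, the sentence still needs correcting.

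A reader might infer four stronger things that the documents do not support:
- That the ITT analysis is nominal only. All randomized patients are included, and events before surgery count.
- That a handful of operations would by itself reverse the result. Reversal needs a first event after surgery and a starting estimate close to zero.
- That risk is understated in the arm with more surgery. Background and rationale notes that surgery can have serious complications; if these count as events, complete follow-up could shift the comparison either way.
- That the Outcomes section already settles the imaging question. Its exclusion may refer only to lesions operated on before entry.

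**Conclusion.** The point holds in a limited form. The contradiction is on the page and needs no assumption. If the surgery sentence is followed as written, outcomes between surgery and month 24 go uncollected for a disease-related reason in an open-label trial, and last status stands in for them. The affected data are first ICH/FND after surgery, mainly in patients operated on for seizures, mass effect or deficits that predate the trial, together with later MRI, seizure and questionnaire results.

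One missing primary event would be worth 5.0 or 2.5 points against a 5.05-point target. Whether any would be missing depends on a surgery rate and a post-surgical risk that the documents do not give. Under the assumptions shown, the chance of at least one is about 14% to 39%. The direction of any bias cannot be determined.

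**What to change.** Reconcile the two sentences so that CCM surgery does not end outcome follow-up. Specifically:
- Keep operated patients in the scheduled visits to month 24 for ICH/FND, seizures, questionnaires and MRI, subject to their consent.
- Count adjudicated ICH/FND regardless of surgery in the main ITT analysis.
- State that lesions operated on during the trial leave the lesion-level imaging analysis from the date of surgery, while the patient stays in it.
- Report surgery by arm with its reason.

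A sensitivity analysis counting surgery as an unfavourable outcome is optional.

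The cost is a short amendment and visits that are already scheduled. Some post-surgical events, including surgical complications, will need adjudication. The Trial status section reports 57 patients included by the end of April 2019, so any patient already removed after surgery may need recontact and possibly renewed consent. With the first inclusion in March 2018, no patient had reached month 24 by then.

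The change concerns data collection and analysis only. Whether and when to operate, and the handling of study drug around surgery, are left to the sponsor.

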#### Statistical analyses

The main analysis will be performed according to an intention-to-treat (ITT) approach. Therefore, all patients randomized in the study will be included in the analysis. As we cannot conduct inferential statistics on the data collected in the pilot study, we will only compare the proportions of adverse events between the groups to assess the safety of propranolol [42]. A per-protocol analysis is foreseen.

Baseline characteristics will be presented by treatment groups, and descriptive statistics will be performed to assess the success of randomization. Kaplan–Meier curves will be constructed to illustrate the occurrence of adverse events in the study over time.

Concerning the analysis of this pilot study, we are only interested in whether the treatment estimate is larger or smaller than zero. Consequently, it is not necessary to formally undertake a hypothesis test of the results. An extension of the trial in the case of encouraging preliminary results is foreseen. Special care will be paid to the biologic consistency of the different endpoints, even if none of them will yield statistically significant differences.

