## Methods/design

### Aims

The purpose of this exploratory pilot trial is to test whether 2-year treatment with propranolol in addition to standard care can reduce the incidence of clinical events, as compared to standard care in patients with FCCMs. Furthermore, this trial will help to set up future clinical trials in an area where there is to date no approved drug reducing the progression of CCM lesions, and will pave the way to study the mechanisms underlying the possible therapeutic role of propranolol in CCMs.

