### Sample size

To the best of the available knowledge, the 2-year risk of CCM-related events (ICH and FND) was estimated at 10.1% in CCM patients receiving recommended standard care [1]. Upon performing a formal sample size calculation, 834 patients should be included in the study to demonstrate a risk reduction of 50% with a power of 80% at a significance level of one-tailed α = 0.05. This estimate is unrealistic both for the over-optimistic treatment effect size and for the number of patients to be included, incompatible with a rare disease.

Therefore, in order to obtain preliminary data, a pilot study is planned, adopting a confidence interval approach, rather than using the more usual power and statistical significance method [40]. The sample size calculation for the pilot trial is driven by the proposed sample size of the main trial. According to the nature of the pilot study design, an 80% one-sided confidence interval is chosen, instead of the 95% two-sided interval usually considered for formal comparative trials. With 60 patients randomized in a 2:1 propranolol:control ratio, in the absence of a reduction of adverse events, a clinically meaningful effect, defined as ≥50% reduction of the 2-year risk of CCM-related events, can be excluded by the defined 80% upper confidence interval. Otherwise, the study will provide a promising signal of activity.

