## Abbreviations

AE: Non-serious adverse event
CCM: Cerebral cavernous malformation
CEC: Clinical Event Committee
DCEP: Dynamic contrast enhanced permeability
DSMB: Data Safety and Monitoring Board
e-CRF: Electronic case report form
FCCM: Familial form of cerebral cavernous malformation
FND: Focal neurological deficits
GCP: Good Clinical Practice
ICH: Intracerebral haemorrhage
IRFMN: Istituto di Ricerce Farmacologiche IRCCS-Mario Negri
ITT: Intention to treat
MRI: Magnetic resonance imaging
PROBE: Prospective, randomized, open-label, blinded endpoint
QSM: Quantitative susceptibility mapping
SADR: Serious adverse drug reaction
SAE: Serious adverse event
SWI: Susceptibility weighted imaging

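### The Statistical analyses section contradicts the 80% one-sided confidence bound on which the 60 patients were justified, and labels the only between-group comparison as a safety comparison of adverse events

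*Protocol article*

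**What the plan says.** Aims: the purpose is "to test whether 2-year treatment with propranolol in addition to standard care can reduce the incidence of clinical events". Outcomes makes new symptomatic ICH or FND, excluding seizures, the primary endpoint.

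Sample size: "the 2-year risk of CCM-related events (ICH and FND) was estimated at 10.1% in CCM patients receiving recommended standard care". A formal trial is costed first, with a one-sided type I error of 0.05 and power in per cent: "834 patients should be included in the study to demonstrate a risk reduction of 50% with a power of 80". That is judged unrealistic, and the pilot is sized by a confidence interval approach in which "an 80% one-sided confidence interval is chosen, instead of the 95% two-sided interval usually considered for formal comparative trials". A reading rule follows. With 60 patients allocated 2:1 and no reduction observed, the bound is to exclude a reduction of 50% or more. Otherwise the result counts as a promising signal.

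Statistical analyses: inferential statistics are said not to be possible, and "we will only compare the proportions of adverse events between the groups to assess the safety of propranolol". Later, "we are only interested in whether the treatment estimate is larger or smaller than zero", so no hypothesis test is needed. The section adds that biological consistency across endpoints will be given special attention. It mentions neither the 80% interval nor ICH/FND.

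Abbreviations: "AE: Non-serious adverse event".

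**The concern.** A one-sided confidence bound is an inferential quantity. If inference is ruled out and only the sign of the estimate is of interest, the bound that justifies 60 patients is not used. An analysis plan written from one section would conflict with the other, so this is more than detail left to a later document.

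The second difficulty is what is compared. The aim and the primary endpoint concern a reduction of ICH/FND, but the comparison is described as one of adverse events to assess safety. The article uses that term in two senses. In the two-step description under Design and in Sample size it stands for ICH/FND. In Follow-up phase and in Quality control and trial monitoring it covers drug side effects and safety reporting. The Kaplan–Meier curves in Statistical analyses carry the same ambiguity.

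At stake is how the pilot is read. The same data could be called promising under one section and unfavourable or neutral under the other, and that reading feeds the decision about an extension or a larger trial.

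**Working it through.** **Inputs** (Sample size and Design): 2-year control risk p = 0.101; target 50% reduction, i.e. 0.0505; 40 propranolol and 20 control; one-sided 80% bound, z = 0.8416. No dropout figure is given and none is applied.

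**1. The formal size of 834.** Two proportions, 2:1, one-sided 0.05, power 80%, unpooled variance:

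- variance term = 0.101 × 0.899 + (0.0505 × 0.9495)/2 = 0.1148
- controls = 0.1148 × (1.6449 + 0.8416)² / 0.0505² = 278.2
- total = 3 × 278.2 = 834.7 (837 if each arm is rounded up)

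The figure of 834 reproduces.

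**2. The pilot size of 60.** With equal risks of 10.1%, the 80% one-sided lower bound for the risk ratio is

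exp{−0.8416 × √[((1 − p)/p) × (1/n_C + 1/n_T)]}.

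- N = 60 (20 and 40): 0.503
- N = 59 (same 1:2 split): 0.4998

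So 60 is the smallest size at which the bound lies above 0.50. The article does not give this formula. The match is a reconstruction, but a close one.

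**3. The same rule on the risk difference.**

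- half-width = 0.8416 × √[0.101 × 0.899 × (1/20 + 1/40)] = 0.8416 × 0.0825 = 0.069, or 6.9 points
- difference to be excluded: 10.1 − 5.05 = 5.05 points

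Sixty patients do not meet the rule on this scale. About 114 would be needed: (0.8416/0.0505)² × 0.101 × 0.899 × 4.5 = 113.5.

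**4. How the two rules read the same data.** Exact enumeration of Binomial(20, 0.101) × Binomial(40, p_T). The bound rule uses the log risk ratio, adds 0.5 when an arm has no events, and calls a result promising when the lower bound does not exceed 0.50.

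| True effect | Sign favours propranolol | Tie | Sign opposes | Bound rule promising | Rules disagree |
|---|---|---|---|---|---|
| None (p_T = 0.101) | 42.3% | 12.1% | 45.6% | 46.2% | 5.3% |
| Halving (p_T = 0.0505) | 67.6% | 11.8% | 20.7% | 79.6% | 12.1% |
| 1.5-fold risk (p_T = 0.1515) | 23.1% | 9.2% | 67.8% | 22.0% | 3.2% |

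A tie counts here as not favourable. Under a true halving, 8.9 of the 12.1 points are ties that the bound rule calls promising (mainly 1 of 20 against 2 of 40, bound 0.366). The other 3.2 points are outright conflicts (0 of 20 against 1 of 40: the sign opposes propranolol, yet the bound is 0.392).

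**5. Expected events.** 60 × 0.101 = 6.06 with no effect; 20 × 0.101 + 40 × 0.0505 = 4.04 with a true halving.

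**The case against.** The strongest reply has three parts.

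First, a reader might infer that the primary endpoint has been replaced by, or pooled with, side effects such as bradycardia. The documents do not support that. Design calls ICH and FND adverse clinical events and has such events centrally adjudicated, Sample size uses the shorter term for the same outcome, and the Abstract rests interpretation on the direction of effect on the primary outcome. The Abbreviations entry distinguishes AE from SAE, while the analysis section writes the words out. The likeliest reading includes ICH/FND. What remains is an ambiguous term and a purpose labelled safety where the aim is efficacy.

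Second, a reader might infer that restoring the bound would cure a near coin toss. It would not. With no effect the bound rule is promising in 46.2% of trials and the sign rule favourable in 42.3%; with a 1.5-fold risk the figures are 22.0% and 23.1%. The noise comes from about six expected events, and the article acknowledges the pilot's limits.

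Third, the sign is not a stand-alone go/no-go rule. The analysis section adds consistency across endpoints, the two-step description adds MRI findings, and the Discussion leaves continuation to the Steering Committee. Declining a hypothesis test also fits an interval approach.

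All three stand as limits on the point. None removes the conflict: a section that rules out inference and attends only to the sign leaves no place for the bound on which the size was chosen.

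**Conclusion.** The point holds as a contradiction within the article, together with an ambiguous outcome term and a mislabelled purpose. The size of 60 reproduces as the smallest that satisfies the interval rule on the risk ratio (0.503 against 0.4998 at 59), and the analysis section then sets that interval aside.

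The practical effect is moderate. The rules conflict in 12.1% of trials under a true halving, 5.3% under no effect and 3.2% under a 1.5-fold risk. The material difference is sensitivity to a true halving, 79.6% against 67.6%. These figures assume the article's 10.1% control risk, full 2-year follow-up of 40 and 20 patients, the log risk ratio, and 0.5 added for zero cells. Another interval method would change them.

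It would go too far to say that the trial cannot answer its aim: ICH/FND is defined, adjudicated and countable by arm. For a declared exploratory pilot this should be fixed, but it does not invalidate the trial.

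**What to change.** Revise Statistical analyses along these lines:

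- Name the 2-year risk of adjudicated ICH/FND by arm, in all randomised patients, as the main comparison.
- Report it as a risk ratio with its 80% one-sided bound, read against the 50% reduction in Sample size, and state how zero-event arms are handled. On this scale the relevant limit is the lower one for the ratio, which is the upper one for the reduction; say so.
- Make the risk ratio the governing scale, because 60 patients meet the rule there and not on the risk difference. Give the difference as description only. The present reference to zero leaves the scale open.
- Delete the statements that inference cannot be conducted and that only the sign is of interest. No hypothesis test need be added.
- Reconcile this with the Step 1 wording under Design. There, no difference in events together with MRI improvement leads to the second step; in Sample size, the absence of a reduction is meant to exclude a worthwhile effect.
- Use CCM-related events for the primary outcome throughout, and tabulate safety AEs and SAEs separately.

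The cost is wording and a little analysis code. The bound will be wide with about six events, and the report should say so.
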